### Outcomes

2.6

The time points for the outcome measurements are presented in detail in Table 1.

#### Primary outcome

2.6.1

The primary outcome will be the mean change in the SNOT-22 score from baseline to 8 weeks.^[17]^ The SNOT-22 is a validated, rhinosinusitis-specific, quality-of-life instrument comprising 22 items encompassing 4 subscales: nasal symptoms, ear and facial symptoms, sleep condition, and psychological domains.^[18]^ The participants will be asked to score a list of 22 symptoms and mark the 5 most important items.

#### Secondary outcomes

2.6.2

The secondary outcomes will include the mean change in the Total Nasal Symptom Score (TNSS), EuroQoL 5 Dimensions 5 Levels (EQ-5D-5L) score, Nasal Endoscopy Index, Lund-Mackay score, and total serum immunoglobulin E (IgE) level. The TNSS assesses 4 nasal symptoms (nasal obstruction, rhinorrhea, itching, and sneezing) on a 4-point scale: 0, no symptoms; 1, mild symptoms; 2, moderate symptoms; and 3, severe symptoms.^[19]^ The EQ-5D-5L questionnaire is brief, consisting of 5 questions and a 5-point scale that documents the patient's overall health status.^[20]^ The Nasal Endoscopy Index was developed and validated for the assessment of nasal cavity conditions from 4 aspects: color, edema or atrophy, dryness or dampness, and the amount and characteristics of rhinorrhea. The patients’ nasal cavities will be examined with a nasal endoscope at every visit. Photos of the anterior nasal cavity will be obtained using the KAU-3000 HARMONY ENT treatment unit (KASAMA ENT Co, Ltd., Incheon, Republic of Korea), and the acquired photos will be scored according to assessment guidelines for the Nasal Endoscopy Index.^[21]^ The Lund–Mackay score is a widely used method for radiological staging of CRS.^[22]^ CT images of the paranasal sinuses and ostiomeatal complex will be scored from 0 to 2 (0, no abnormality; 1, partial opacification; and 2, complete opacification) by an independent radiology specialist. We will also examine the total serum IgE level to evaluate the immune-regulatory effects of GGTCS.

#### Other measures

2.6.3

Participants will also be asked to complete the cold-heat pattern identification questionnaire and Korea Sasang Constitutional Diagnostic Questionnaire-15 (KS-15) at the first visit in order to identify the correlation between the efficacy of GGTCS, the cold-heat pattern, and the Sasang constitutional type.

### Randomization and allocation concealment

2.7

A statistician will generate random allocation numbers using a computer program [Strategic Applications Software (SAS), version 9.4; SAS Institute Inc., Cary, NC]. The generated numbers will be sealed in opaque envelopes and stored in double-locked cabinets. Participants who fulfil all inclusion criteria will be assigned to 1 of the 2 groups via blocked randomization.

### Blinding

2.8

The participants, investigators, coordinators, pharmacist, monitoring agent, and statistician will be blinded to the group allocation data, which will be known only to the person in charge of random allocation. The statistician will create a random allocation table indicating assignment to group A or B. The person in charge of random allocation will deliver this allocation table and group information to the pharmaceutical company (because there is no resource to create a randomization list at the investigational products manufacturing company, our team will prepare the randomization table). The pharmaceutical company will make and label the investigational products on the basis of this information. The label will include each participant's identification number (R1001 to R1058; identical to the random allocation numbers) and visit number (V1, V2, V3, and V4). An opaque emergency envelope containing allocation information will be prepared and stored in a safe place in anticipation of unexpected events. Violation of blinding will be considered only under circumstances where knowledge of the medication being administered to a participant is essential for treatment. The validity of blinding will be assessed according to the new blinding index.

### Sample size

2.9

No clinical trial has been conducted to evaluate the effects of GGTCS on the SNOT-22 score for patients with CRS. A formal power calculation has not been performed because this study will evaluate the feasibility to calculate a required sample size for subsequent definitive randomized clinical trials. On the basis of recommendations by a previous study,^[23]^ a minimal effect size of 0.25 and dropout rate of 20% have been assumed for this trial. Thus, a total of 58 participants, 29 in each group, will be recruited.

### Data and safety monitoring

2.10

Regular monitoring will be conducted to ensure quality control of the data according to the planned protocol and standard operating procedures. Data quality will be ensured by regular monitoring. The monitoring agent will confirm whether the data are consistent with the source documents and whether the trial is conducted according to the approved protocol. All AEs observed during the study period will be recorded and reported. In case severe AEs and crucial issues occur, the investigators will determine whether these issues are acceptable and whether the trial should be amended or ended. The trial data will be saved in an electronic data capture system (Medidata Rave; Medidata Solutions Inc., New York, NY).

### Safety and adverse events

2.11

For the safety of the study participants, complete blood cell counts, liver function tests, lipid tests, and urine analyses will be performed during the screening phase and at the end of the trial. Vital signs will be examined at every visit. Contact information for AE reporting at any time will be provided to all participants.

AEs associated with GGTCS have not yet been revealed. However, it is assumed that pseudoaldosteronism, myopathy, rash, pruritus, anorexia, gastric discomfort, nausea, diarrhea, autonomic dysfunction, and voiding dysfunction can occur in association with the individual herbal components of GGTCS. Any AE reported by participants will be recorded in the “Adverse Event Record Table.” A causal relationship between the event and GGTCS or placebo treatment will be evaluated using a 6-point scale: 1, definitely related; 2, probably related; 3, possibly related; 4, probably not related; 5, definitely not related; and 6, unknown. The seriousness of AEs will be scored using a 3-point scale: 1, mild; 2, moderate; and 3, severe. Any AEs will be reported in accordance with the regulations of the institutional review board (IRB).

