#### Exclusion criteria

2.4.2

The exclusion criteria will be as follows:

(1)A previous history of nose-related or allergy-related diseases and treatmentA.Nasal polyps, cystic fibrosis, primary ciliary dyskinesia, untreated deviated nasal septumB.Acute bacterial exacerbation of CRS (acute pain, acute pressure, fever, pus on discharge)C.Acute complication of CRS (abscess)D.Orbital or central nervous system complications of CRSE.Acute respiratory infection developed within the last 7 daysF.Use of topical decongestants or cromolyn sodium within the last 3 daysG.Use of antibiotics, antihistaminics, anticholinergics, and intranasal steroids within the last 1 weekH.Use of oral steroids or leukotriene receptor antagonists within the last 4 weeksI.Receipt of immunotherapy within the last 5 years(2)Presence of serious medical conditions that could interfere with clinical trial participationA.Uncontrolled hypertension (systolic blood pressure ≥ 160 mm Hg and diastolic blood pressure ≥ 100 mm Hg);B.Uncontrolled diabetes mellitus (HbA1c ≥ 6.5%);C.Abnormal kidney function test results showing blood creatinine levels that are more than twice the upper limit of the normal range;D.Abnormal liver function test results showing alanine aminotransferase or aspartate aminotransferase levels that are more than twice the upper limit of the normal range;E.Serious hyperlipidemia, anemia, active tuberculosis, thyroid disease, and other serious inflammatory and systemic diseases;F.Past or present history of malignant tumors.(3)Pregnancy, planning a pregnancy, or breastfeeding(4)Hypersensitivity to the investigational drug or any of its components(5)Participation in other clinical trials within the past 1 month(6)Communication difficulties that will not allow proper compliance with the investigator's instructions(7)Ineligibility for participation as judged by the investigator

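### The safety panel in section 2.11 lists no electrolytes and no creatine kinase, although the same section anticipates pseudoaldosteronism and myopathy, so symptom-free cases could be missed or seen only non-specifically.

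*Protocol article*

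**What the plan says.** Section 2.11 (Safety and adverse events) gives the laboratory tests done to protect participants: "complete blood cell counts, liver function tests, lipid tests, and urine analyses will be performed during the screening phase", and again when the trial ends. It adds two further routes of detection: "Vital signs will be examined at every visit" and "Contact information for AE reporting at any time will be provided to all participants". Section 2.10 adds that "All AEs observed during the study period will be recorded and reported".

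The second paragraph of 2.11 says that adverse events of the formula itself are not yet known. It then names those expected from its ingredients: "it is assumed that pseudoaldosteronism, myopathy, rash, pruritus, anorexia, gastric discomfort", followed by four more.

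Other sections call for blood tests that 2.11 does not mention. The exclusion criteria (2.4.2) use creatinine ("Abnormal kidney function test results showing blood creatinine levels") and HbA1c, and the secondary outcomes (2.6.2) include an immunoglobulin: "We will also examine the total serum IgE level". The exclusion criteria also show what the liver tests contain: "Abnormal liver function test results showing alanine aminotransferase or aspartate aminotransferase levels".

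**The concern.** The panel and the list of expected harms stand in adjacent paragraphs, and for the first two harms they do not match. Most of the other eight, such as rash, nausea or diarrhoea, are things a participant can notice and report. Pseudoaldosteronism and myopathy differ in that a laboratory change can come before any symptom. The natural tests are serum potassium (or an electrolyte panel) for the first and creatine kinase for the second. That link is general medical knowledge and is not stated in the protocol article.

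Safety is part of the stated objective (2.1), and the Discussion expects the results to support larger trials of safety and efficacy. Dosing is three times daily for 8 weeks (2.5), and participants may continue established medication for chronic disease. If the trial later reported no pseudoaldosteronism and no myopathy, that statement would rest on no specific laboratory measurement. Without an entry value, an abnormality found by chance during the trial could not be told apart from one already present.

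**Working it through.** The plan gives no figure to reproduce here. The check sets the named harms against the stated tests.

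1. **Harms named in 2.11.** Pseudoaldosteronism, myopathy, rash, pruritus, anorexia, gastric discomfort, nausea, diarrhoea, autonomic dysfunction and voiding dysfunction: 10 in all. The point concerns the first 2.

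2. **Stated detection routes against these two harms.**

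| Route (section) | Pseudoaldosteronism | Myopathy |
|---|---|---|
| Blood counts (2.11) | not specific | not specific |
| Liver function, including ALT and AST (2.11, 2.4.2) | not specific | a muscle-enzyme rise may raise AST; not specific |
| Lipids (2.11) | not specific | not specific |
| Urine analysis (2.11) | not specific | possible signal; not specific |
| Vital signs at every visit (2.11) | a rise in blood pressure may show; not specific | not specific |
| Adverse event reporting and recording (2.10, 2.11) | clinically apparent cases can be recorded | clinically apparent cases can be recorded |
| Serum potassium or electrolytes | not listed | – |
| Creatine kinase | – | not listed |

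Specific tests listed for the two harms: 0 of 2.

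3. **What is left unmeasured under the stated panel.** A low potassium with normal blood pressure, and an isolated rise in creatine kinase. Other symptom-free cases might show through blood pressure, aminotransferases or urine, but those signals would not point to the cause.

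4. **Is 2.11 the complete list of blood tests?** No. Creatinine and HbA1c are needed for eligibility and total IgE is an outcome, and all three lie outside it. They serve entry and efficacy, however, so they do not show that further safety tests exist.

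5. **Timing.** The study period is 8 weeks of medication and follow-up (2.2), so end of trial is week 8. Blood is already drawn at both time points for the stated panel.

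6. **Size of the addition.** 58 participants × 2 tests × 2 time points = 232 assays at most in randomised participants, counting electrolytes as one test. Screening assays in people who are not randomised come on top; their number is not given.

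**The case against.** The strongest reply is that this argues from silence in a condensed article. Section 2.11 names groups of tests rather than individual analytes, the schedule in Table 1 is not shown, and three blood tests demonstrably lie outside the 2.11 list. A missing mention is therefore weak evidence that a test is not done. The harms are only assumed from individual ingredients, and naming a possible harm does not promise a dedicated assay for it.

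Much of this stands as a limit. It makes the fix conditional on what Table 1 and the full protocol contain, and it rules out calling the text contradictory. It does not dispose of the point. The article does not leave the safety panel to another document: it states a panel and, directly after it, harms that the panel does not specifically address.

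A reader might infer that clinically apparent cases would certainly be caught and silent ones at week 8 certainly would not. The document supports neither half. It provides for recording adverse events but sets no targeted check, so apparent cases could be reported but detection is not guaranteed. Blood pressure, AST/ALT and urine analysis could give a non-specific signal in some silent cases, and the two tests may be in the material not shown.

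A reader might also want a percentage for the harm that could go unseen. The document gives no frequency for either condition. A zero-event upper limit for an arm of 29 would describe the sample size and not what the omission costs, so none is offered.

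**Conclusion.** The point holds as a modest, inexpensive improvement to safety measurement. As stated in 2.11, the panel has no specific test for 2 of the 10 harms the section anticipates. Symptom-free cases could be missed or seen only non-specifically. The primary outcome and its analysis are not affected.

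This rests on two assumptions: that potassium or electrolytes and creatine kinase are the relevant tests, and that neither is already in Table 1 or the full protocol. If the second fails, the point falls away. Confidence is low for that reason, and the matter is one for the sponsor to consider.

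**What to change.** First check Table 1 and the full protocol. If the tests are not there, add one line to 2.11: serum potassium or an electrolyte panel, and creatine kinase, on the blood samples already taken at screening and week 8. Summarise screening-to-week-8 changes and counts outside the laboratory's reference range by arm, descriptively. No formal test is needed at this sample size, and no clinical threshold or treatment rule is proposed.

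This would show an abnormality present at week 8 and whether it was already there at entry. Two time points would not show a transient abnormality in mid-treatment.

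The cost is at most 232 routine assays in randomised participants, those in screen failures, and some incidental abnormal values to follow up. No extra visit or blood draw is needed.

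If the tests are not added, the free alternative is to limit any report that these two harms were absent to clinically apparent cases.

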At any time during the clinical trial, the participant may voluntarily withdraw from the clinical trial or also be discontinued at the researcher's discretion. If at any time during the clinical trial period, an adverse event (AE) determined to be harmful to the participant is observed, the researcher may temporarily discontinue the treatment of that participant. If continuing the trial is harmful to the participant based on the progression of the AE and its causal relationship with the drug, then the researcher will permanently discontinue the clinical treatment of that participant. Anyone who is discontinued early from the study due to an AE may receive the appropriate treatment for the AE, when necessary. Anyone who is discontinued early from the study owing to an AE must be assessed continuously by the researcher or someone designated by the researcher until the AE is resolved or is determined to be permanent.

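### Section 2.11 records an intensity grade under the name seriousness, and section 2.10 ties trial-level review to severe events, so a serious event of lower intensity is not marked serious and does not clearly prompt that review

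*Protocol article*

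**What the plan says.** Three places in the protocol article deal with the grading and handling of AEs.

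- **Section 2.11 (Safety and adverse events)** sets the grading: "The seriousness of AEs will be scored using a 3-point scale: 1, mild; 2, moderate; and 3, severe". It adds a causality rating, "A causal relationship between the event and GGTCS or placebo treatment will be evaluated using a 6-point scale", and says that any AE is reported under the IRB's regulations.
- **Section 2.10 (Data and safety monitoring)** sets the trial-level review: "In case severe AEs and crucial issues occur, the investigators will determine whether these issues are acceptable". The same sentence lets them decide whether the trial is changed or stopped. Just before it, the section says: "All AEs observed during the study period will be recorded and reported".
- **Section 2.4.2 (Exclusion criteria), closing paragraph**, covers the individual participant. The condition is harm: "If at any time during the clinical trial period, an adverse event (AE) determined to be harmful to the participant is observed", in which case treatment may be interrupted and later stopped for good. A participant withdrawn because of an AE "must be assessed continuously by the researcher or someone designated by the researcher until the AE is resolved" or judged permanent.

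The article nowhere defines a serious AE by its outcome.

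**The concern.** Severity and seriousness are different variables. Severity says how intense an event is. Seriousness says whether it had, or threatened, a particular kind of outcome. Neither determines the other: an event that leads to hospital admission can be moderate in intensity, and a severe headache can pass without consequence.

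Section 2.11 does not leave seriousness to another document. It says how seriousness will be scored, and the scale it gives measures something else. Section 2.10 then uses the top word of that scale in the condition for reconsidering the trial.

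Safety is an aim alongside efficacy (section 2.1), and the Discussion wants the results to support larger trials of both. Section 2.11 says that the AEs of the formula are not yet known and lists pseudoaldosteronism and myopathy among those that might occur. For such a trial, a count of serious events by arm is a basic safety result. A variable that carries the name seriousness but holds intensity grades cannot supply it.

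**Working it through.** No formula applies and the article states no figure on this point. The check is to follow events through the rules as printed.

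**Step 1: the recorded score.** Two illustrative events, not taken from the article:

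| Event | Serious by outcome? | Intensity | Score under section 2.11 |
|---|---|---|---|
| Leads to hospital admission, moderate intensity | yes | moderate | 2 |
| Severe headache that resolves without consequence | no | severe | 3 |

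The score for seriousness ranks the non-serious event above the serious one. No cut-off on the scale separates serious from non-serious events, because outcome does not enter the score.

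**Step 2: the trial-level condition in section 2.10.** It has two parts, severe AEs and crucial issues, and only the first matches a grade in section 2.11.

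- The first event, scored 2, does not meet the AE part.
- If the two parts are read as alternatives, the event is reviewed only if someone judges it to be a crucial issue. That term has no definition, so the result rests on discretion.
- If the joining word is read literally, both parts are needed. The first event then fails, and even a severe AE would not be enough alone.

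On neither reading does the text clearly bring the first event to trial-level review. On the alternative reading it does not exclude it either.

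**Step 3: routes that do not depend on the grade.**

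| Provision | Reaches the first event? | Marks it as serious? | Addresses amending or ending the trial? |
|---|---|---|---|
| All AEs recorded and reported (2.10) | yes | no | no |
| Reporting under IRB regulations (2.11) | yes | possibly, if those regulations define it | not stated |
| Causality rating (2.11) | yes | no, it rates relatedness | no |
| Harm-based handling of the participant (2.4.2) | if judged harmful | no | no, it concerns that participant's treatment |
| Follow-up after withdrawal for an AE (2.4.2) | if withdrawn | no | no |

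The event is therefore captured and can be acted on for the participant. Two things remain open: the variable that should identify it as serious does not, and its path to the trial-level decision is unclear.

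**The case against.** The strongest reply is that this is a slip of naming. A mild/moderate/severe scale is plainly a severity scale, and nothing printed says that grade 3 defines a serious AE or that grades 1 and 2 escape the handling of serious events. The article condenses a fuller protocol (version 1.1). Neither that protocol, the Adverse Event Record Table nor the electronic forms are shown, and any of them, or the IRB regulations, may hold an outcome-based definition and a yes/no field.

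Much of this stands, and it rules out several stronger readings that a reader might infer:

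- *Such an event goes unreviewed.* Not supported. The grade-independent routes apply, and the undefined second part of the section 2.10 condition might cover it.
- *Section 2.10 holds the only safety trigger.* Not supported. Section 2.4.2 has a harm-based trigger for the participant. Section 2.10 is only the sole trial-level one printed.
- *The trial cannot report serious AEs by arm.* Not established. The printed scale alone cannot yield that count, but an unseen form might.
- *One miscoded event is 1/29 = 3.4% of an arm.* The arithmetic is right, but this is the weight of any one participant. It says nothing about how likely or how important miscoding is.

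The reply does not remove the point itself. Leaving a definition to the full protocol would be an omission and no finding. Here the article prints an operative scoring rule under the wrong name, and a second operative sentence uses a word from that scale. A naming slip in a safety rule still directs whoever fills in the form.

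**Conclusion.** The point holds in limited form. Section 2.11 calls an intensity scale seriousness, and section 2.10 links the decision on the trial's future to severe AEs and undefined crucial issues. Followed as written, a serious event of mild or moderate intensity is not identified as serious by this scale and does not clearly lead to trial-level review. It is still recorded, reported to the IRB under its rules, rated for causality and open to action for the participant.

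Its size cannot be put in numbers, since the article gives no expected rate of serious events. The conclusion assumes the usual trial meaning of the two terms and that the printed wording is what staff would apply. If the full protocol or the form already keeps the two apart, what remains is an inconsistency in the published text. Correction is worthwhile because it costs very little and concerns a stated aim of the trial.

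**What to change.** 1. In section 2.11, rename the 3-point scale severity (intensity). Record seriousness separately as yes/no, using an outcome-based definition. If the full protocol or the record form already has that field, align the article with it.
2. Reconcile section 2.10 with section 2.11. The trigger should say whether it means severity, seriousness or both, and crucial issues should be defined, so that serious events of lower intensity are not left out by wording alone. What should lead to amending or ending the trial is for the sponsor and investigators to decide.
3. Report severity and seriousness by arm as two separate summaries.

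The cost is at most one extra field on the AE form, some wording changes and one additional line in the safety tables. Sample size, visits and the efficacy analysis are unaffected.
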